# Central corneal thickness changes in bevel-up versus bevel-down phacoemulsification cataract surgery: study protocol for a randomised, triple-blind, parallel group trial

**DOI:** 10.1136/bmjopen-2016-012024

**Published:** 2016-09-29

**Keywords:** central corneal thickness, endothelial damage, phaco tip position, phacoemulsification

## Abstract

**Introduction:**

Corneal endothelial damage following phacoemulsification is still one of the major concerns of modern day cataract surgery. Although many techniques have been proposed, the risks of posterior capsular rupture and corneal endothelium damage persist. In theory, damage to the corneal endothelium is minimised by delivering the lowest phaco energy only in the direction necessary to emulsify the lens nucleus. Hence, it is believed that the bevel of the needle should be turned towards the nucleus or the nuclear fragment (ie, bevel-down. However, there is a difference of opinion among ophthalmologists with reference to the phaco tip's position (bevel-up vs bevel-down) during phacoemulsification. This subject has not been extensively studied earlier.

**Methods and analysis:**

This is a prospective, triple-blinded (trial participant, outcome assessor and the data analyst), randomised controlled trial with 2 parallel groups and with an allocation ratio of 1:1. It will be conducted in a tertiary care hospital, Mangaluru, India. The objective is to compare the postoperative central corneal thickness changes between the bevel-up and bevel-down techniques of phacoemulsification. Patients aged >18 years with immature cataract undergoing phacoemulsification will be selected for the study. The important exclusion criteria are the history of previous significant ocular trauma or intraocular surgery, corneal pathology, pseudoexfoliation syndrome, intraocular inflammation, a preoperative fully dilated pupil <6 mm, anterior chamber depth <2.5 mm and nuclear sclerosis grade >4. After randomisation, patients will undergo phacoemulsification surgery either by a bevel-up or bevel-down procedure. With an estimated power of 80%, the calculated sample size is 55 patients in each group. The recruitment will start from April 2016.

**Ethics and dissemination:**

Yenepoya University Ethics Committee, India has approved the study protocol (YUEC/148/2016 on 18 February 2016). It complies with the Declaration of Helsinki, local laws and the International Council for Harmonization-good clinical practices.

**Trial registration number:**

CTRI/2016/02/006691; Pre-results.

Strengths and limitations of this studyThis study attempts to find the most cornea-friendly technique of clear corneal phacoemulsification with regard to phaco tip's position.Study findings would be more pertinent to those who are at high risk of corneal decompensation (ie, small pupil, short anterior chamber depth, high nuclear grade, large nucleus, older age, etc) following phacoemulsification.Multiple factors can affect the study outcome (central corneal thickness).

## Introduction

Corneal endothelial damage following phacoemulsification is still one of the major concerns of modern day cataract surgery. Introduction of different techniques and certain innovations in the phaco instrumentation have reduced the incidence of postoperative corneal endothelial loss. At every stage of cataract surgery, the surgeon has options to optimise corneal endothelial safety. This includes relevant parameters in various phaco platforms, surgical techniques, materials used and patient characteristics such as the grade of the cataract, age of the patient and the presence of corneal disease.

Several mechanisms have been proposed for endothelial cell damage during phacoemulsification; these include mechanical contact with nuclear fragments, irrigation flow, turbulence and movement of fluid, direct trauma caused by instruments or lens fragments, and formation of cavitation bubbles.^1^
^2^

In phacoemulsification procedures the most important predictor of corneal clarity in the early postoperative period is inversely proportional to the amount of ultrasound energy used. For this reason, all of the major platforms now use power modulation to reduce the amount of phaco power necessary, either by varying the duty cycle and pulse energy or by varying the pulse intervals with microburst techniques.

Several phacoemulsification techniques have been developed and modified.^3–7^ Although many techniques have been proposed, the risks of posterior capsular rupture and corneal endothelium damage persist. In theory, damage to the corneal endothelium is minimised by delivering the lowest phaco energy only in the direction necessary to emulsify the lens nucleus. Furthermore, phacoemulsification should occur in the posterior chamber rather than in the iris plane or the anterior chamber.^8^ Hence, it has traditionally been believed that the bevel of the needle should be turned towards the nucleus or the nuclear fragment (ie, bevel-down).^9^ However, Faramarzi *et al*^10^ hypothesise that in the bevel-up technique, the phaco tip, and therefore the source of heat, are farther from the endothelial cells than in the bevel-down technique and this decreases the chance of endothelial cell damage. Further another clinical trial by Raskin *et al*^11^ concluded in their study that bevel-up tip position has a negative effect on corneal endothelial cells compared with the bevel-down position. Hence, there is a difference of opinion among ophthalmologists with respect to the phaco tip position during phacoemulsification. This subject has not been extensively studied earlier, hence this study is planned.

## Objective

To compare the postoperative central corneal thickness (CCT) changes between bevel-up and bevel-down techniques of phacoemulsification.

*Trail design*: Prospective randomised, parallel group, exploratory, triple-blind (trial participant, outcome assessor and the data analyst) trial with an allocation ratio of 1:1.

*Trial registration*: This trial is registered prospectively in the Clinical trial registry of India (CTRI/2016/02/006691) and the full trial protocol can be accessed on http://ctri.nic.in/Clinicaltrials/showallp.php?mid1=14144&EncHid=&userName=CTRI/2016/02/006691.

### Participants and methods

*Inclusion criteria*: Consecutive patients aged >18 years with immature cataract undergoing phacoemulsification at Yenepoya Medical College Hospital, Mangaluru, India will be selected for the study.

*Exclusion criteria*: History of previous significant ocular trauma or intraocular surgery, corneal pathology, pseudoexfoliation syndrome, intraocular inflammation, a preoperative fully dilated pupil smaller than 6 mm, anterior chamber depth (ACD) <2.5 mm and nuclear sclerosis grade >4. Cases with intraoperative complications, those where direct chop could not be done and patients not willing to participate in the study will be excluded.

### Surgical procedure

Two limbal stab incisions will be made. The anterior capsule will be stained with trypan blue dye after which, the anterior chamber will be filled with hydroxypropyl methylcellulose 2%. A capsulorhexis 5.0–5.5 mm in diameter will be created with a needle cystotome. A 2.8 mm clear corneal incision will be made, followed by hydrodissection and hydrodelineation of the nucleus.

Phacoemulsification of the nucleus will be performed using the phaco chop technique with a 30° 19-gauge phaco tip. In both groups, the nucleus will be stabilised with the phacoemulsification tip, which is impaled with moderate vacuum and low ultrasonic power. The chopper will be advanced under the anterior capsule until it can pass around the equator of the nucleus at the nucleus–epinucleus border, 180° from the phaco tip. The chopper will be advanced towards the phaco tip splitting the nucleus into half. By rotating the lens, several pieces of nucleus are broken (chopped). The pieces will then be emulsified. Following this, irrigation/aspiration of cortical material will be performed with a bimanual irrigation/aspiration cannula. Next, a foldable hydrophilic acrylic intraocular lens with ultraviolet absorbing optic and square edge design (Acryfold, Appasamy ocular devices, Pondicherry, India) will be implanted in the capsular bag using a disposable injector cartridge system. Finally, the anterior chamber will be irrigated, the ocular viscoelastic device will be removed, the wounds will be secured by stromal hydration and the eye will be patched.

#### Phaco parameters

All the operations will be performed with Sovereign compact phacoemulsification system with WhiteStar technology and Ellips (Abbott Medical Optics, Abbott Laboratories, Abbott Park, Illinois, USA). During direct chop, the parameters will be kept as follows: maximum aspiration flow rate: 28 cc/min, maximum vacuum: 295 mm Hg and threshold vacuum: 125 mm Hg; maximum power: 30 continuous 6/12 (33%) with Whitestar on and occluded 40 linear long pulse 6/12 (33%) with Whitestar on. The parameters for higher grades of cataract will be as follows: maximum aspiration flow rate: 28 cc/min, maximum vacuum: 400 mm Hg and threshold vacuum 250 mm Hg; maximum power: 40 continuous 6/12 (33%) with Whitestar on and occluded 40 linear long pulse 6/12 (33%) with Whitestar on.

### Intraoperative evaluation

The parameters to be evaluated intraoperatively include mean phaco power (%), effective phaco time (EPT) (seconds) and phaco time using Ellips FX technology (EFX). The EFX is roughly the EPT with a specific coefficient for the transversal movement of the phaco tip expressed in seconds. Amount of irrigating fluid used will also be noted.

### Postoperative evaluation

All the patients will be put on topical ciprofloxacin and dexamethasone eye drops combination, one drop six times a day for 1 week for the first week, after which it will be gradually tapered over a period of 1 month. All the patients will be examined postoperatively on day 1, day 7 and at the end of 1 month. The examinations will include UDVA, CDVA, slit lamp biomicroscopy, applanation tonometry, funduscopy and CCT measurement. Telephonic reminders will be made to encourage the complete follow-up.

*Outcome measure*: The CCT will be measured on days 1, 7 and 30. Deturgescence of the corneal stroma is controlled by the pumping action of the endothelial layer and can be monitored by the measurement of CCT. Loss or damage of endothelial cells leads to an increase in corneal thickness, which may ultimately induce corneal decompensation and loss of vision.^13^ A significant linear correlation exists between increase in corneal thickness in the immediate postoperative period and percentage of endothelial cell loss.^14^ Hence, CCT measurement can be used as a simple tool to assess the amount of corneal endothelial damage postcataract surgery.

Figure 1 shows the proposed flow of the participants in this trial.

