**Figure 1 BMJOPEN2016012024F1:**
[figure not shown]
Flow diagram of the trial participants. ACD, anterior chamber depth.

*Sample size calculation*: The sample size calculation is based on the anticipated differences in the CCT (mean±SD) between the two groups. A sample of 50 in each group is needed to detect a mean CCT difference of 20 µm with an SD of 35.3,^15^ 1:1 allocation ratio, α error of 0.05 and a power of 80%.^16^ The final sample is inflated to 55 with due consideration of 10% attrition.

*Sensitivity analysis of sample size calculation for CCT*: The power of the study will be estimated based on the actual number of the study participants who complete the study and the observed differences in CCT across the two study groups.

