## Data collection and statistical analysis

A detailed statistical analysis plan will be prepared. A blind review of the data will be performed after the end of the planned follow-up period without looking at the randomised treatment for each trial participant. Attritions will be excluded from the analysis. Intention-to-treat principle will be used for the analysis. Results will be expressed in proportion and means (±SD) for categorical and continuous variables, respectively. Student's t-test will be used to compare CCTs between the study groups. A repeated measures analysis of variance will be conducted to assess for any difference in CCT between bevel-up and bevel-down groups over time. All the data will be analysed using SPSS V.16.

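### CCT is measured at three visits and analysed by two methods with no primary comparison, although the sample size assumes one test; if any result may be claimed at 0.05, the false positive chance is roughly 7% to 17%

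*Protocol article*

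**What the plan says.** All references are to the Protocol article.

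- **Objective:** "To compare the postoperative central corneal thickness (CCT) changes between bevel-up and bevel-down techniques of phacoemulsification". No day is named. The same section labels the trial exploratory.
- **Postoperative evaluation, outcome measure:** "The CCT will be measured on days 1, 7 and 30". CCT is the only item listed there, and no visit is ranked above the others. In support of CCT as a marker, the section says: "A significant linear correlation exists between increase in corneal thickness in the immediate postoperative period and percentage of endothelial cell loss".
- **Sample size calculation:** the trial is sized to "detect a mean CCT difference of 20" µm with SD 35.3 and 1:1 allocation, at an "error of 0.05 and a power of 80"%. No visit is attached to the difference or to the SD. The 50 per group is raised to 55 for 10% attrition.
- **Data collection and statistical analysis:** "Student's t-test will be used to compare CCTs between the study groups", and then "A repeated measures analysis of variance will be conducted to assess for any difference in CCT between bevel-up and bevel-down groups over time". Neither is called primary. The section says that a detailed analysis plan will be prepared.

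**The concern.** A sample size calculation describes one test. This one has an effect, an SD, an alpha and a power, but the document does not identify the comparison they belong to. Three visits and two methods are available, and the ANOVA alone can supply a group effect and a group-by-time effect.

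Two things are at stake. First, the 80% power cannot be attributed to a particular day or analysis, so a reader cannot tell what 55 per group is able to show. Second, if the investigators may report whichever comparison reaches 0.05, the overall chance of a false claim exceeds the stated 5%. The results could then be read in either direction by choosing a visit. That matters for a question on which, according to the article's Introduction, published opinion is already divided.

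**Working it through.** **1. Reproduce the plan's own figure.** Inputs from the Sample size calculation: difference 20 µm, SD 35.3, alpha 0.05, power 80%, 1:1. Sidedness is not stated.

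Normal approximation, two-sided: n = 2 × (1.960 + 0.842)² × 35.3² / 20² = 2 × 7.85 × 1246.09 / 400 ≈ 48.9, so 49 per group. The exact noncentral t calculation gives 49.9, so 50, with power 80.1% at 50 per group. A one-sided test would need 39. The stated 50 is therefore one two-sided comparison, and 50 × 1.1 = 55. The figure is sound for a single test.

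**2. Chance of at least one false positive if any test may be claimed at 0.05.** As a reference, three independent tests give 1 − 0.95³ = 0.143.

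The visits are measured on the same eyes, so the tests are correlated. The document gives no correlation, so a range is assumed. The simulation had no true difference, 50 per group, three visits with a common correlation ρ, and 20,000 trials per value of ρ. It used two-sided t-tests at each visit and the ANOVA group and group-by-time tests (Greenhouse-Geisser), all at 0.05. The Monte Carlo standard error at 0.15 is √(0.15 × 0.85 / 20,000) ≈ 0.0025.

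| ρ (assumed) | Three t-tests | + ANOVA group effect | + ANOVA group-by-time | + both ANOVA terms |
|---|---|---|---|---|
| 0 | 0.144 | 0.163 | 0.152 | 0.171 |
| 0.5 | 0.127 | 0.132 | 0.152 | 0.157 |
| 0.7 | 0.107 | 0.108 | 0.141 | 0.142 |
| 0.8 | 0.095 | 0.096 | 0.132 | 0.133 |
| 0.9 | 0.083 | 0.083 | 0.122 | 0.122 |
| 0.95 | 0.073 | 0.073 | 0.116 | 0.116 |

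The extremes are 0.073 (0.073 / 0.05 ≈ 1.5 times alpha) and 0.171 (0.171 / 0.05 ≈ 3.4 times).

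Sensitivity of this range:
- A separate run of 40,000 trials per correlation gave 0.141, 0.124, 0.110 and 0.098 for three t-tests at ρ = 0, 0.5, 0.7 and 0.8, in close agreement.
- Entering the preoperative reading as a fourth ANOVA time point changes little: 0.115 to 0.178 with both terms, the top value again at ρ = 0.
- A correlation that decays between visits (0.5 to 0.9 for adjacent visits) gives 0.126 to 0.156 with both terms.

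**3. Cost of the alternatives.** If all three visits were tested with a Bonferroni split, each at 0.05 / 3 = 0.0167, power for 20 µm at 50 per group would fall to about 65%. Restoring 80% would need 67 per group by the t-test, or 67 × 1.1 ≈ 74 with attrition. Naming one primary comparison at 0.05 leaves 50 (55) unchanged.

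**4. Effect of adjusting for preoperative CCT.** If 35.3 is the SD of CCT at the chosen visit and r is its correlation with preoperative CCT, the residual SD is 35.3 × √(1 − r²), which cannot exceed 35.3. For example, an assumed r of 0.5 gives 35.3 × 0.866 ≈ 30.6. On that condition the unadjusted calculation is conservative for an adjusted test.

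**The case against.** A reader might infer that a t-test is planned at every visit, that each test is run at 0.05, and that the false positive rate is therefore two to three times alpha. The document does not support that as a statement of fact. Alpha appears only in the sample size paragraph, and the t-test sentence names no visits. The ANOVA could be read as the overall test, with the t-tests as its description by visit. Nothing says that any significant result counts as success. The multiple also moves with an unknown correlation: with t-tests alone and ρ of 0.9 or more it is only about 1.5 to 1.7. These points stand, and the size must be stated conditionally.

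It can also be said that the trial is labelled exploratory, that the full protocol is said to be at the registry, and that a detailed analysis plan is to follow. Test levels, hierarchies and multiplicity rules properly belong in such a plan, and their absence here is not the point. The visit behind the 20 µm is different. It is an input to a calculation printed in this document, and it decides what the stated power means. An exploratory label does not fit with a formal alpha and power statement that is meant to be taken at face value.

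Finally, a reader might infer from the rationale about the immediate postoperative period that later CCT is uninformative, or that day 1 must be primary. The same section goes on to recommend CCT in general terms as a measure of endothelial damage, so days 7 and 30 are not excluded. The rationale favours day 1 but does not compel it. Nor does the document show which visit the cited SD describes.

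**Conclusion.** The point holds in conditional form. The document fixes a sample size for one two-sided comparison but identifies neither the visit nor the analysis, so its 5% error rate and 80% power attach to no defined test. That conclusion needs no simulation.

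The size of the possible error inflation is roughly 7% to 17%. It rests on three assumptions: that any significant visit or analysis could be claimed, that each would be judged at 0.05, and that the between-visit correlation lies somewhere from 0 to 0.95. For three t-tests alone the range is about 7% to 14%; with both ANOVA terms it is about 12% to 17%. Every value exceeds 5%.

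**What to change.** Before unblinding, name one primary comparison in the protocol and the analysis plan: CCT at a single stated visit, adjusted for the preoperative CCT already collected, tested once at two-sided 0.05. Day 1 is the visit best supported by the document's own rationale, but the sponsor may choose another single visit or a single longitudinal test.

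State which visit the 20 µm and the SD of 35.3 refer to. Report the other visits and the longitudinal model as secondary, as estimates with 95% confidence intervals and not as alternative routes to a positive conclusion.

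The cost is a few sentences. The 50 (55) per group need not change, provided that 35.3 is the SD of CCT at the chosen visit; if it describes something else, the calculation should be rechecked. The downside is that a difference seen only at a non-primary visit becomes supportive.

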**Figure 1 BMJOPEN2016012024F1:**
[figure not shown]
Flow diagram of the trial participants. ACD, anterior chamber depth.

*Sample size calculation*: The sample size calculation is based on the anticipated differences in the CCT (mean±SD) between the two groups. A sample of 50 in each group is needed to detect a mean CCT difference of 20 µm with an SD of 35.3,^15^ 1:1 allocation ratio, α error of 0.05 and a power of 80%.^16^ The final sample is inflated to 55 with due consideration of 10% attrition.

*Sensitivity analysis of sample size calculation for CCT*: The power of the study will be estimated based on the actual number of the study participants who complete the study and the observed differences in CCT across the two study groups.

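### The sample size states no allowance for patients removed after randomisation because of events in surgery, and that removal conflicts with intention-to-treat; the 10% inflation is also one patient per arm short

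*Protocol article*

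**What the plan says.** The sample size calculation in the protocol article states: "A sample of 50 in each group is needed to detect a mean CCT difference of 20" µm, with an SD of 35.3, equal allocation, and "α error of 0.05 and a power of 80"%. It continues: "The final sample is inflated to 55 with due consideration of 10% attrition". The abstract repeats the result: "With an estimated power of 80%, the calculated sample size is 55 patients in each group". Attrition is not defined and no inflation formula is given.

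Three other places bear on how many patients will be analysed:

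- **Participants and methods, exclusion criteria:** "Cases with intraoperative complications, those where direct chop could not be done and patients not willing to participate in the study will be excluded".
- **Abstract, Methods and analysis:** surgery follows randomisation.
- **Data collection and statistical analysis:** "Attritions will be excluded from the analysis". The next sentence adopts the intention-to-treat principle.

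**The concern.** There are two separate problems.

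The first is arithmetic. To have 50 left after losing 10%, one divides by 0.9. Adding 10% to 50 gives a number that falls just short once the 10% is lost.

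The second concerns who is counted. A complication in surgery or a failed chop can be known only once the operation is under way, so those patients have already been randomised and belong to the 55. The protocol removes them, the sample size section does not mention them, and the analysis section names a principle under which they would stay.

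At stake is some power, by an amount the documents do not let us fix, and also the comparison itself. If tip position affects how often a complication occurs or a chop fails, removing those cases leaves two groups that are no longer the randomised ones. Eyes that had a difficult operation may also be the ones with the most corneal swelling, which is what the trial measures.

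**Working it through.** **Inputs.** From the sample size calculation: difference 20 µm, SD 35.3, α 0.05, power 80%, 1:1 allocation, 50 per arm before and 55 after 10% attrition. The test is taken from the analysis section: "Student's t-test will be used to compare CCTs between the study groups". Sidedness is not stated. Two-sided is assumed because it reproduces 50; one-sided gives 39.

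**Reproducing the 50.**

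- Normal approximation: n = 2 × [35.3 × (1.960 + 0.842) / 20]² = 48.9, so 49 per arm.
- Exact two-sided t-test (noncentral t, noncentrality 20 / (35.3 × √(2/n)), 2n − 2 degrees of freedom): power is 79.3% at 49 and 80.1% at 50, so 50 per arm.

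The stated 50 is reproduced by the exact t-test.

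**Inflation.**

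- 50 × 1.10 = 55, the stated figure.
- 50 / 0.9 = 55.6, so 56.
- 55 × 0.9 = 49.5 remaining, against 50 needed.
- Largest loss from 55 that leaves 50: 5 / 55 = 9.1%.
- Power at 49.5 per arm: 79.7% by the exact t-test, 80.5% by the normal approximation.
- Cost of the slip: 80.1% − 79.7% = 0.4 points.

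**Intraoperative exclusions.** The documents give no rate, so the rates below are assumptions. Here the removals come on top of the full 10%, with losses added:

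| Assumed extra removal | Total loss | Left per arm | Power (exact t) |
|---|---|---|---|
| none (10% covers everything) | 10% | 49.5 | 79.7% |
| 5% | 15% | 46.75 | 77.4% |
| 10% | 20% | 44 | 74.8% |

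Compounding the losses changes little:

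- 5% extra: 55 × 0.9 × 0.95 = 47.0, power 77.6%.
- 10% extra: 55 × 0.9 × 0.9 = 44.6, power 75.3%.
- 2% extra: 55 × 0.9 × 0.98 = 48.5, power 78.9%.

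**The analysis set.** The exclusion criteria drop complicated and failed-chop cases, the abstract puts surgery after randomisation, and the analysis section applies intention-to-treat. Under that principle a randomised patient is not dropped because of what happened in the operation. The exclusion rule and the principle cannot both be followed for these patients.

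**The case against.** The strongest reply is that 55 is adequate. Power of 79.7% rounds to the stated 80%. A planner starting from the normal-approximation figure would get 49 / 0.9 = 54.4, so 55. That disposes of any claim that the arithmetic alone costs the trial its power. It does not make the written step right, because the protocol starts from 50.

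A reader might also infer that the 10% covers loss to follow-up only. The documents do not say so. Attrition is undefined and could include patients removed at surgery, in which case power stays near 80%. What stands is narrower: no allowance for these removals is stated, and on either reading 55 tolerates 9.1% loss, not 10%.

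A reader might further infer that every excluded case arises once the tip is in its allocated position. The surgical procedure does not support that. The incisions, capsulorhexis and hydrodissection come before phacoemulsification, and a complication can occur at any of them. These events still fall after randomisation, which is all the point needs.

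Finally, the intention-to-treat sentence may mean that these cases will be kept, and the protocol plans to re-estimate power from the number who complete. The first would remove the problem, but the exclusion criteria say the opposite and one of the two must give way. The second reports the completed number afterwards; it does not settle who is analysed.

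**Conclusion.** The point holds in two parts of unequal weight.

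The inflation slip is real and immaterial: 56 rather than 55 per arm, and about 0.4 points of power. It does not show that the trial lacks its stated 80%.

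The more important part is that the protocol removes randomised patients for events in surgery, states no allowance for them, and also names intention-to-treat. That these removals occur after randomisation, and that they conflict with the principle, follows from the text. The size of any power loss does not. The range of about 77% to 75% rests on an assumed 5% to 10% removal on top of a full 10% attrition, with a two-sided test and the protocol's own difference and SD. It shows sensitivity and is not a forecast.

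This is a minor correction to the sample size statement, joined to a conflict over the analysis set that should be settled before the data are unblinded.

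**What to change.** 1. In the exclusion criteria and the analysis section, state that patients with intraoperative complications or a failed direct chop stay in the primary analysis in the arm to which they were randomised. An analysis without them should be a sensitivity analysis at most. This reconciles the two sections, protects the randomised comparison and removes most of the possible shortfall in numbers. The patients are already enrolled and the protocol examines all patients on days 1, 7 and 30, so the cost is to keep measuring them. Their results may be more variable than the SD of 35.3 assumes, so the gain in power may be less than the head count suggests.

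2. In the sample size calculation, say what attrition covers and replace the inflation sentence with wording such as: *55 per arm retains 50 analysed per arm if total loss from all causes, including any removal for events during surgery, is at most 9%.* If the authors prefer to keep the 10% rule, the figure is 56 per arm, 112 in total instead of 110.

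The cost is a few sentences. With the restated tolerance no extra patients are needed.

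### The planned post-trial power estimate uses the observed CCT difference, so it largely restates the p-value and does not check the sample size assumptions

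*Protocol article*

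**What the plan says.** All the design inputs are in the sample size paragraph of the protocol article, below Figure 1. The target is given as "A sample of 50 in each group is needed to detect a mean CCT difference of 20 µm". The variability comes next ("with an SD of 35.3"), then the allocation ("1:1 allocation ratio"), then the error rates ("α error of 0.05 and a power of 80"%). Loss to follow-up is allowed for thus: "The final sample is inflated to 55 with due consideration of 10% attrition".

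The next paragraph carries the run-in heading "Sensitivity analysis of sample size calculation for CCT". Its content is a single plan: "power of the study will be estimated based on the actual number of the study participants who complete the study and the observed differences" (between arms, for CCT). It names no SD for this calculation, does not keep the 20 µm design difference, and does not say how the resulting figure will be used.

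Under Data collection and statistical analysis, the between-group test is given: "Student's t-test will be used to compare CCTs between the study groups". The same section plans a blind review of the data after follow-up and says that a detailed analysis plan will be prepared.

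**The concern.** A sensitivity analysis of a sample size calculation should ask whether the assumptions behind it held: was the SD near 35.3, did about 50 per arm finish, and what power did the trial therefore have for 20 µm? Putting the observed difference in place of 20 µm answers another question. It evaluates power as if the true effect equalled the estimate, and with the observed SD that number is fixed by the p-value and the group sizes. It adds nothing to the test result.

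What is at stake is how a non-significant result is read. The Introduction motivates the trial by conflicting earlier work on tip position, so a small difference is a plausible and useful finding. A low power figure printed beside it could suggest that the trial was too small to tell, when the confidence interval may already rule out the difference the trial was sized to detect.

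**Working it through.** **Inputs.** From the sample size paragraph: design difference 20 µm, SD 35.3 (unit not printed, taken as µm), α 0.05, power 80%, 50 per arm, 55 after inflation. From the analysis section: two-sample Student's t-test. Sidedness is not stated; two-sided is assumed because it reproduces the stated number (one-sided gives 39 per arm).

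**1. The protocol's own figure.** Normal approximation: n = 2 × 35.3² × (1.960 + 0.842)² / 20² = 48.9, so 49 per arm. Exact non-central t power is 79.3% at 49 and 80.1% at 50, so 50 is the exact t-test answer. Inflation: 50 × 1.10 = 55. The sample size is not in question.

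**2. Power at the observed difference, using the observed SD.** Let t = d / (s√(2/n)), with d the observed difference and s the observed SD. Observed power is the chance that a non-central t variable with 2n − 2 df and non-centrality |t| falls outside ± the critical value. At n = 50 there are 98 df and the critical value is 1.984. The only data input is |t|, which also fixes p.

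| Two-sided p | t (98 df) | Difference at SD 35.3 (µm) | Observed power |
|---|---|---|---|
| 0.05 | 1.984 | 14.0 | 50.2% |
| 0.10 | 1.661 | 11.7 | 37.6% |
| 0.20 | 1.290 | 9.1 | 24.8% |
| 0.50 | 0.677 | 4.8 | 10.3% |

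At p = 0.20 the answer is 24.8% whether the SD is 20, 35.3 or 60. With 55 per arm, these four values change by less than 0.1 percentage point. Every result with p > 0.05 therefore has observed power of at most about 50%. Observed power reaches 80% only at p of about 0.0057 or less, so significant results with p between about 0.006 and 0.05 also fall below 80%.

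**3. The same calculation with the planned SD.** If 35.3 is kept while the observed SD differs, a result at p = 0.05 has d = 1.984 × SD × √(2/50):

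- observed SD 25: d = 9.9 µm, power 28.5%;
- observed SD 35.3: d = 14.0 µm, power 50.2%;
- observed SD 45: d = 17.9 µm, power 70.7%.

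The observed SDs of 25 and 45 are assumptions, to show the range. The tie to p is no longer exact, but a non-significant result reaches 80% only if the observed SD exceeds about 50 µm.

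**4. Against the confidence interval.** At SD 35.3 and 50 per arm the standard error is 35.3 × √(2/50) = 7.06 µm, and the 95% half-width is 1.984 × 7.06 = 14.0 µm.

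- Observed difference 5 µm: interval −9.0 to 19.0 µm; observed power 10.8%.
- Observed difference 5.9 µm: interval −8.1 to 19.9 µm; observed power 13.1%.

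Both intervals exclude 20 µm while observed power is far below 80%.

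**5. Power at the fixed 20 µm.** Non-centrality is 20 / (SD × √(2/n)), exact t:

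| Completers per arm | SD 35.3 |
|---|---|
| 40 | 70.6% |
| 45 | 75.7% |
| 50 | 80.1% |
| 55 | 83.8% |

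At 50 per arm it would be 91.0% with SD 30 and 69.7% with SD 40 (both SDs assumed, to show the range). These figures move with the achieved number and the SD, which are the planning assumptions, and not with the observed difference.

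**The case against.** The strongest reply is that this is one ancillary sentence in a trial described as exploratory. It changes no test, error rate, sample size or estimate, and the harm needs a later misreading. That is right about scale. It does not remove the point, because the protocol itself names the observed difference as the input; this is a stated method and not detail left to the analysis plan.

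Several stronger readings are tempting, and the documents do not support them.

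- A reader might infer that the protocol would declare every non-significant result underpowered. It gives no threshold, label or use for the figure. The shortfall against 80% is arithmetic, not a planned rule.
- A reader might infer that the trial could not then support a negative conclusion. An extra power figure blocks no confidence interval. Group means, SDs and numbers are enough to form one, and not spelling it out here is no fault when an analysis plan is to follow.
- A reader might say the figure always equals a transform of p. That holds only if the observed SD is used, and the paragraph names no SD.
- A reader might object to using the number who complete. For a power check the achieved number is the sound half of the sentence, provided it is paired with a fixed difference. How attrition is handled in the main analysis is a separate matter.

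It also stands that the protocol presents 20 µm as an anticipated difference, not as an equivalence margin or a minimally important difference. An interval that excludes 20 µm shows that the planned effect is not supported; it does not by itself show that the techniques are equivalent.

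**Conclusion.** The concern holds in a limited form. The planned estimate is observed power. It adds essentially nothing to the p-value and does not do what its heading promises. At 50 per arm, non-significant results would show at most about 50% if the observed SD is used, and below 80% with the planned SD unless the observed SD exceeds about 50 µm. At SD 35.3 this happens even where the interval excludes 20 µm, as it does for observed differences up to about 5.9 µm (20 − 14.0 = 6.0).

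This rests on a two-sided test at 0.05, equal arms and an SD in µm. The consequence is confined to interpretation, chiefly of a null result. It is worth correcting because the correction is nearly free, not because it threatens the validity of the comparison.

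**What to change.** Replace the sentence so that power is recomputed at the fixed 20 µm, using the achieved number per arm and the observed within-group SD, which is set beside 35.3. The within-group SD needs treatment labels, so this belongs after unblinding. If the check is wanted at the blind review, use the total SD and note that it slightly overstates the within-group SD: with a true 20 µm difference and equal arms it would be about √(35.3² + 10²) = 36.7.

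State that the result will be interpreted through the between-group difference and its 95% confidence interval, set against the planned 20 µm. This needs no change to the planned t-test.

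The cost is a short rewording, with no new data, visits or participants.
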